## Abstract

**Introduction:**

Chronic heart failure (CHF) is associated with frequent hospitalizations, poor quality of life, and high healthcare costs. Despite therapeutic progress, early recognition of clinical deterioration remains difficult. The SMART-CARE study investigates whether artificial intelligence (AI)-enabled remote monitoring using CE-certified wearable devices can reduce hospital admissions and improve patient outcomes in CHF.

**Methods:**

SMART-CARE is a prospective, multicenter, observational cohort study enrolling 300 adult patients with CHF (HFrEF, HFmrEF, or HFpEF) across three Italian tertiary centers. Participants are assigned to an intervention group, using wrist-worn, chest-worn, and multiparametric CE-certified wearable devices for six months, or to a control group receiving standard CHF care. Physiological data (e.g., SpO₂, HRV, respiratory rate, skin temperature, sleep metrics) are continuously collected and analyzed in real time through AI algorithms to generate alerts for early clinical intervention. The primary endpoint is a ≥20% reduction in hospital admissions over six months. Secondary outcomes include changes in quality of life (Kansas City Cardiomyopathy Questionnaire), biomarkers (BNP, NT-proBNP, renal function, electrolytes), echocardiographic indices (LVEF, LV volumes), and safety events.

**Results:**

We hypothesize that AI-driven remote monitoring will significantly reduce hospitalizations, improve quality of life, and favorably impact biochemical and echocardiographic parameters compared to standard care.

**Conclusion:**

SMART-CARE is designed to evaluate the clinical utility of multimodal wearable devices integrated with AI algorithms in CHF management. If successful, this approach may transform traditional care by enabling earlier detection of decompensation, optimizing resource utilization, and supporting the scalability of remote monitoring in chronic disease management.

**Clinical Trial Registration:**

ClinicalTrials.gov, identifier NCT06909682.

## Introduction

1

The incidence of chronic diseases is progressively increasing, along with the associated care burden for families, general practitioners, and the National Health System (1–3). Patients affected by chronic conditions are complex and require strong interaction between primary care and specialized centers to ensure proper management of all phases of the disease, such as diagnosis, clinical exacerbation handling, and the definition of an individualized therapeutic program (4). Specifically, chronic heart failure (CHF) is a complex syndrome involving multiple regulatory systems and is associated with high rates of rehospitalization and mortality (5). The complexity of this condition often necessitates frequent access to hospital facilities for multidisciplinary evaluations and diagnostic exams, thereby increasing both direct and indirect costs (lost workdays, travel, inappropriate hospitalizations) (6, 7). For patients with multiple chronic conditions, whose continuous therapies and follow-up visits aim to extend the number of years lived without severe disabilities, it is crucial to create a “territorial network” that facilitates dialogue between local health services and secondary/tertiary care centers (8). This would promote resources optimization and reduce hospital admissions or services. Furthermore, appropriate management during the intervals between outpatient visits is essential. In recent years, there has been a growing adoption of telemedicine solutions, which, through information and communication technologies (ICT), enable the delivery of healthcare services outside traditional healthcare settings, even when the healthcare provider and patient are in different locations (9, 10). Telemedicine is a valuable tool that supports the continuity of care between hospitals and communities, improves access to health services, and optimizes chronic disease management (11, 12). It also helps enhance home care and reduce unnecessary travel, especially for patients living in remote areas (13). ICT is used to facilitate the exchange of information between care partners and to promote patient empowerment by providing devices for self-monitoring of biomedical parameters, which can be remotely monitored by healthcare professionals to tailor the treatment plan (14). CHF, in particular, is characterized by alternating periods of stability and clinical worsening, but over the last three decades, management of this condition has significantly advanced, with pharmacological and device-based therapies (15, 16). Among these, implantable defibrillators, alone or combined with cardiac resynchronization therapy, are equipped with algorithms that monitor signs of congestion through thoracic impedance. Despite their effectiveness, these devices are invasive and require surgical implantation (17, 18). Given the high burden and complexity of CHF, there is an increasing need for complementary data beyond clinical history and physical examination, including telemonitoring and biochemical information (19). In recent years, the most innovative scenario has been represented by disease management supported by wearable and non-invasive medical devices capable of continuously collecting physiological parameters useful for remote monitoring. These technologies are available in different formats—wrist-worn devices, chest sensors, and non-invasive multiparametric monitors—each with specific advantages. Among them, the Empatica EmbracePlus (Empatica Inc.) is a CE-certified wristband capable of recording multiple signals such as blood oxygen saturation (SpO₂), heart rate (HR) and variability (HRV), electrodermal activity (EDA), sleep quality (actigraphy), respiratory rate (RR), temperature, and fatigue detection (20–22). The Movesense MD sensor (Suunto/Kaasa Health) is a CE-marked chest-worn device validated for ECG and motion tracking (23), while the Polar H10 chest strap (Polar Electro), although primarily designed for sports and fitness, provides accurate HR and HRV measurements that can be integrated into telemonitoring programs (24, 25). In addition, a non-invasive multiparametric device allows real-time monitoring of several metabolic and hemodynamic variables (e.g., glucose, hemoglobin, blood pressure, and oxygen saturation), expanding the range of information available for clinical decision-making (26). When integrated with telemedicine platforms, electronic health records, and advanced analytics, these devices enable continuous monitoring, early detection of decompensation, and timely therapeutic adjustments (e.g., diuretic dosage). This comprehensive and patient-centered approach has the potential to improve self-management, optimize healthcare resource utilization, and reduce CHF exacerbations and hospitalizations. However, despite technological progress, most previous telemonitoring studies in CHF have relied on single-parameter measurements, intermittent data collection, or rule-based alert systems (27–29), which limit their ability to detect subtle and individualized early signs of clinical deterioration. Moreover, only a few studies have integrated continuous multimodal wearable signals, and the application of advanced artificial intelligence to real-time physiologic data remains limited (30, 31). SMART-CARE aims to address this knowledge gap by combining high-resolution, multi-sensor wearable data with AI-driven predictive analytics capable of identifying trends, detecting early physiological deviations, and generating personalized alerts. This approach is designed to overcome the limitations of earlier telemonitoring interventions and support a more proactive and individualized model of CHF management.

This study aims to collect foundational data for the development of the “SMART-CARE” project. The project's final goal is to identify relationships and/or mathematical formulas (multimarker scores) among clinical, biochemical, instrumental, and wearable-monitored parameters that can predict the course and prognosis of patients with CHF. Within this study protocol, part of the broader SMART-CARE project, the objective is to assess whether remote monitoring using a wearable, mini-invasive device can reduce hospitalizations in patients with CHF.

## Methods

2

### Study design and population

2.1

The SMART-CARE study is a multicenter, prospective, observational cohort trial, designed to evaluate the clinical utility of artificial intelligence (AI)-enabled remote monitoring in patients with CHF. A prospective, non-randomized observational design was chosen for both ethical and pragmatic reasons. Allocation to the intervention group required patients' explicit willingness to use the wearable device and to undergo continuous monitoring, making randomization unfeasible. To minimize potential selection bias, statistical adjustment methods (multivariable regression, propensity score matching, and stratified analyses by age, sex, New York Heart Association class - NYHA, Left Ventricular Ejection Fraction - LVEF phenotype, and comorbidities) will be applied. The trial will be conducted across three tertiary care centers in Italy: AOU “San Giovanni di Dio Ruggi d'Aragona”, IRCCS Neurolesi “Bonino Pulejo”, and IRCCS Fondazione Casa Sollievo della Sofferenza. The study will enroll 300 adult patients (≥18 years) with a confirmed diagnosis of CHF, including Heart Failure with reduced Ejection Fraction (HFrEF), Heart Failure with mildly reduced Ejection Fraction (HFmrEF), or Heart Failure with preserved Ejection Fraction (HFpEF) for at least six months, who are clinically stable and on optimized medical therapy for at least one month prior to enrolment (Figure 1).

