**Figure 1 F1:**
[figure not shown]
Flow diagram of the study design.

Eligible patients will be stratified into two parallel cohorts based on voluntary consent to participate in the remote monitoring intervention. Patients in the intervention group will wear the EmbracePlus (Empatica Inc.) mini-invasive device continuously for six months (20, 21). This CE-certified wearable device captures a comprehensive set of physiological parameters, including SpO₂, HRV, EDA, respiratory rate, peripheral skin temperature, and sleep quality, which are transmitted in real time to the SMART-CARE digital platform (20–22). The collected data will be processed through AI algorithms capable of identifying abnormal trends and generating alerts to prompt timely clinical action (32–34); moreover, these data will serve a broader purpose within the SMART-CARE project: to support the development of a novel diagnostic and prognostic algorithm. By integrating biometric signals with clinical, instrumental, and biochemical information, the SMART-CARE platform will apply advanced machine learning techniques to generate predictive models aimed at identifying the clinical trajectory of CHF patients and optimizing personalized care strategies.

Patients in the control group will undergo standard chronic heart failure (CHF) follow-up as per clinical guidelines, including in-person visits every three months, electrocardiography (ECG), echocardiography, and laboratory evaluation [e.g., B-type Natriuretic Peptide (BNP), N-terminal pro-B-type Natriuretic Peptide (NT-proBNP), renal and hepatic function, serum electrolytes]. All patients, regardless of group assignment, will be evaluated at baseline, 3 months, and 6 months.

Patients with NYHA class IV symptoms, anticipated heart transplantation or ventricular assist device implantation within 6 months, severe renal impairment (estimated Glomerular Filtration Rate - eGFR <30 mL/min/1.73 m^2^), terminal illness, or inability to comply with study procedures will be excluded (Table 1).

**Table 1 T1:** Inclusion and exclusion criteria for the SMART-CARE study.

Inclusion criteria	Exclusion criteria
Age ≥ 18 years (male or female)	NYHA class IV symptoms
Confirmed diagnosis of CHF ≥ 6 months prior to screening	Planned heart transplant or VAD implantation within 6 months
NYHA functional class I, II, or III	Severe renal impairment (eGFR < 30 mL/min/1.73 m^2^) or dialysis dependency

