Optimized heart failure therapy for at least 1 month prior to enrolment	Terminal illness with limited life expectancy (e.g., metastatic cancer, end-stage lung disease)
Any LVEF phenotype (HFrEF, HFmrEF, HFpEF)	Pregnancy
≥1 hospitalization or outpatient visit with IV therapy for CHF in last 12 months	Dermatological conditions or allergies preventing prolonged use of the wearable device
Ability to provide informed consent or availability of a legally authorized representative	Cognitive or psychiatric disorders impairing adherence to study procedures

CHF, chronic heart failure; eGFR, estimated Glomerular Filtration Rate; HFmrEF, Heart Failure with mildly reduced Ejection Fraction; HFpEF: Heart Failure with preserved Ejection Fraction; HFrEF, Heart Failure with reduced Ejection Fraction; IV, intravenous; LVEF, left ventricular ejection fraction; NYHA, New York Heart Association; VAD, ventricular assist device.

All clinical, instrumental, and biochemical data will be recorded in anonymized case report forms and stored in a secure digital database. Biospecimens (blood and urine) will be collected and retained for secondary biomarker analysis. The study protocol adheres to the Declaration of Helsinki and Good Clinical Practice guidelines, and it was approved by the regional ethics committee (Comitato Etico Campania 2; Approval No. 185867). The trial is registered at ClinicalTrials.gov with the identifier NCT06909682.

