#### Primary endpoint analysis

2.6.1

To assess the primary endpoint of the study, Kaplan–Meier survival curves will be constructed to compare the time to first hospitalization between groups. Group differences will be evaluated using the log-rank test. Subsequently, a Cox proportional hazards regression analysis model will be performed to examine the association between the variable “Device Use (Yes vs. No)” and the reduction in hospital admissions. The model will be adjusted for all statistically significant covariates identified through ANOVA between the two groups. To mitigate selection bias resulting from the non-randomized design, propensity score methods will be applied. The propensity score will be estimated using baseline variables including age, sex, LVEF phenotype, NYHA class, major comorbidities (hypertension, atrial fibrillation, diabetes mellitus, COPD/OSA, obesity), prior HF hospitalizations, baseline biomarkers (BNP/NT-proBNP, renal function, electrolytes), and key echocardiographic indices (LVEF, LV volumes). A 1:1 nearest-neighbour matching approach without replacement will be used. Covariate balance between groups will be evaluated using standardized mean differences (SMD), with values <0.10 indicating adequate balance. Results will be expressed as hazard ratios (HR) with corresponding 95% confidence intervals (CI).

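### The stability requirement in section 2.1 is undefined and absent from Table 1, and the propensity score captures recency of the last heart failure event only partly

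*Protocol article*

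**What the plan says.** Eligibility is stated in two places.

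- **Section 2.1, running text.** The study enrols patients "who are clinically stable and on optimized medical therapy for at least one month prior to enrolment". Stability is not defined in the article. This paragraph does not mention a qualifying event.
- **Table 1.** The corresponding inclusion line is "Optimized heart failure therapy for at least 1 month prior to enrolment"; stability does not appear in it or in any other line. The table adds "≥1 hospitalization or outpatient visit with IV therapy for CHF in last 12 months", with no minimum time between that event and enrolment. It also sets "NYHA functional class I, II, or III".
- **Exclusions in the text.** The list that closes with "terminal illness, or inability to comply with study procedures will be excluded (Table 1") does not bar a recent discharge or recent decompensation. NYHA class IV is excluded.

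Group membership follows the patient's own willingness to use the device (sections 2.1 and 2.2). The primary outcome is hospital admissions, including emergency visits, over six months (section 2.4). It is analysed as time to first hospitalization, with propensity matching (section 2.6.1). The propensity variables that bear on recent heart failure history are NYHA class and "prior HF hospitalizations, baseline biomarkers (BNP/NT-proBNP, renal function, electrolytes"). Neither time since the last event nor outpatient IV treatment is named.

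**The concern.** The two statements of eligibility do not contain the same conditions: the text has one that the table lacks, and the table has one that the text lacks. Where a term is undefined and its duration uncertain, three centres can reasonably apply it differently.

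This bears on the primary comparison because nothing but adjustment protects it. Patients with a recent decompensation plausibly have a higher early risk of admission, and a time-to-first-event analysis is sensitive to early events. If patients approached soon after an event accept the device at a different rate from settled clinic patients, the groups will differ in recency. Part of that difference could then pass for a device effect or mask one.

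**Working it through.** **1. The eligibility wording side by side**

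| Condition | Section 2.1 text | Table 1 |
|---|---|---|
| Clinically stable | Required, undefined | Absent |
| Optimized therapy for at least one month | Required | Required |
| CHF hospitalization or outpatient IV visit | Not mentioned in the paragraph | Required, 0 to 12 months before enrolment |
| NYHA class | IV excluded | I to III; IV excluded |

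**2. Which patients are affected**

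- *Therapy optimized only during a stay in the last month.* This patient fails the one-month therapy condition in both places. There is no conflict.
- *NYHA III, unchanged optimized therapy for two months, IV treatment last week.* This patient meets the Table 1 lines on therapy, NYHA class and qualifying event. Under section 2.1 the answer depends on the reading. If the month governs stability, the patient is out. If it governs therapy alone, stability is needed only at enrolment, and the patient may be in.

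The affected group is therefore patients with a recent event whose therapy was already optimized for a month.

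**3. What the adjustment can see**

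Every enrolled patient has a qualifying event in the past 12 months, so having had one does not separate patients. If prior HF hospitalization were coded yes/no over those 12 months, it would distinguish only those who qualified by admission from those who qualified by an outpatient IV visit. NYHA class and natriuretic peptides carry some information on recency. The stratification factors in section 2.1 (age, sex, NYHA class, LVEF phenotype, comorbidities) add none directly.

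**4. Illustration only; every input is assumed**

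The documents give no admission rate and no distribution of time since the last event. Suppose a six-month admission risk of 20% for patients stable for more than a month, 40% for patients within a month of an event, and no device effect. With a share q of recent patients, group risk = 0.20(1 − q) + 0.40q.

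| Recent, device | Recent, control | Risks | Crude risk ratio |
|---|---|---|---|
| 10% | 30% | 0.22 vs 0.26 | 0.85 |
| 10% | 40% | 0.22 vs 0.28 | 0.79 |
| 0% | 16% | 0.20 vs 0.232 | 0.86 |

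With the imbalance reversed and a true 20% reduction:

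- 40% recent on device, 10% in control: (0.28 × 0.8)/0.22 = 1.02.
- 30% recent on device, 10% in control: (0.26 × 0.8)/0.22 = 0.95.

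Under these risks the ratio simplifies to (1 + q_device)/(1 + q_control). To reach 0.80 with no device effect:

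- q_device = 10% needs q_control = 1.10/0.80 − 1 = 37.5%.
- q_device = 0% needs q_control = 1/0.80 − 1 = 25%.

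For scale, if last events were spread evenly over 12 months (also an assumption), 1/12, or about 8%, would fall in the final month, before the therapy condition removes some. Clustering near enrolment would raise that share. All of these ratios are crude; the planned analysis is matched and adjusted.

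**The case against.** A reader might infer that the article contradicts itself outright, so that anyone just out of hospital is eligible by the table and ineligible by the text. The documents do not support that. Neither place claims to be the complete list, and the two can be applied jointly: a qualifying event within 12 months, and stable at enrolment. The month may attach only to therapy. The therapy condition already removes many recent discharges. An operational definition of stability may well stand in the full protocol, which is not shown.

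On confounding, the propensity list is introduced as an open one and includes NYHA class, BNP/NT-proBNP, renal function and prior HF hospitalizations, all of which may partly stand in for recency. How prior hospitalizations are coded is analysis-plan detail. A covariate-adjusted Cox model is also planned, and section 5 acknowledges selection bias. It would be wrong to say that matching is blind to recency.

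Most of this stands. What remains is that the article prints two eligibility statements that differ on stability and leaves the scope of the month open. It also accepts outpatient IV events as qualifying without naming them in the adjustment. Proxies are a weaker safeguard than the variable itself, particularly when that variable is at hand from eligibility checking.

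**Conclusion.** The point holds as an incomplete criteria table, an undefined term, and a gap in the named adjustment variables. It is not a flat contradiction.

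The eligibility ambiguity affects a limited group. The confounding concern rests on two assumptions that are plausible but not shown in the documents: that recency of the last event affects admission risk, and that it differs between patients who accept and patients who decline the device.

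The size of any bias cannot be derived from the documents. A reader might take the 0.79 in the illustration as evidence that the trial could meet its own 20% criterion through imbalance alone. That needs large assumed imbalances, an assumed doubling of risk, and no help from the planned adjustment. Other equally assumed inputs give 0.85 or 0.86, short of the criterion. The case for acting is that the safeguard is almost free in a self-selected cohort with an admission endpoint.

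**What to change.** 1. Reconcile the section 2.1 text and Table 1 on stability: carry the requirement into the table or remove it from the text, define the term, and state whether the month applies to it. Whether there is a minimum interval since the last event, and how long, is for the sponsor to decide; no interval is proposed here.
2. Record the date and type (hospitalization or outpatient IV visit) of the most recent qualifying event at baseline. Checking the 12-month criterion already requires this information.
3. Add time since that event, and its type, to the propensity variables in section 2.6.1, and report their standardized mean differences with the others.

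Cost: a wording change in one or both places, a date and a type field on the baseline form, and one or two more propensity covariates. The extra covariates may slightly reduce the number of matched pairs.

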**Figure 1 F1:**
[figure not shown]
Flow diagram of the study design.

Eligible patients will be stratified into two parallel cohorts based on voluntary consent to participate in the remote monitoring intervention. Patients in the intervention group will wear the EmbracePlus (Empatica Inc.) mini-invasive device continuously for six months (20, 21). This CE-certified wearable device captures a comprehensive set of physiological parameters, including SpO₂, HRV, EDA, respiratory rate, peripheral skin temperature, and sleep quality, which are transmitted in real time to the SMART-CARE digital platform (20–22). The collected data will be processed through AI algorithms capable of identifying abnormal trends and generating alerts to prompt timely clinical action (32–34); moreover, these data will serve a broader purpose within the SMART-CARE project: to support the development of a novel diagnostic and prognostic algorithm. By integrating biometric signals with clinical, instrumental, and biochemical information, the SMART-CARE platform will apply advanced machine learning techniques to generate predictive models aimed at identifying the clinical trajectory of CHF patients and optimizing personalized care strategies.

Patients in the control group will undergo standard chronic heart failure (CHF) follow-up as per clinical guidelines, including in-person visits every three months, electrocardiography (ECG), echocardiography, and laboratory evaluation [e.g., B-type Natriuretic Peptide (BNP), N-terminal pro-B-type Natriuretic Peptide (NT-proBNP), renal and hepatic function, serum electrolytes]. All patients, regardless of group assignment, will be evaluated at baseline, 3 months, and 6 months.

Patients with NYHA class IV symptoms, anticipated heart transplantation or ventricular assist device implantation within 6 months, severe renal impairment (estimated Glomerular Filtration Rate - eGFR <30 mL/min/1.73 m^2^), terminal illness, or inability to comply with study procedures will be excluded (Table 1).

**Table 1 T1:** Inclusion and exclusion criteria for the SMART-CARE study.

Inclusion criteria	Exclusion criteria
Age ≥ 18 years (male or female)	NYHA class IV symptoms
Confirmed diagnosis of CHF ≥ 6 months prior to screening	Planned heart transplant or VAD implantation within 6 months
NYHA functional class I, II, or III	Severe renal impairment (eGFR < 30 mL/min/1.73 m^2^) or dialysis dependency
Optimized heart failure therapy for at least 1 month prior to enrolment	Terminal illness with limited life expectancy (e.g., metastatic cancer, end-stage lung disease)
Any LVEF phenotype (HFrEF, HFmrEF, HFpEF)	Pregnancy
≥1 hospitalization or outpatient visit with IV therapy for CHF in last 12 months	Dermatological conditions or allergies preventing prolonged use of the wearable device
Ability to provide informed consent or availability of a legally authorized representative	Cognitive or psychiatric disorders impairing adherence to study procedures

CHF, chronic heart failure; eGFR, estimated Glomerular Filtration Rate; HFmrEF, Heart Failure with mildly reduced Ejection Fraction; HFpEF: Heart Failure with preserved Ejection Fraction; HFrEF, Heart Failure with reduced Ejection Fraction; IV, intravenous; LVEF, left ventricular ejection fraction; NYHA, New York Heart Association; VAD, ventricular assist device.

All clinical, instrumental, and biochemical data will be recorded in anonymized case report forms and stored in a secure digital database. Biospecimens (blood and urine) will be collected and retained for secondary biomarker analysis. The study protocol adheres to the Declaration of Helsinki and Good Clinical Practice guidelines, and it was approved by the regional ethics committee (Comitato Etico Campania 2; Approval No. 185867). The trial is registered at ClinicalTrials.gov with the identifier NCT06909682.

